#### Environmental monitoring of pollutants at study sites

Pollutants for assessment in both environmental and human matrices were selected based upon their relevance to viscose rayon and associated chemical manufacturing industry identified through review of previously published literature [9].

*i) Monitoring of gaseous pollutants in ambient air*. The ambient air monitoring will be carried out in the study area (see Fig 2) for identified gaseous pollutants viz., CS_2_, H_2_S, HCl, Cl_2_, and SO_2_ using a factory calibrated, electrochemical sensor based multi-gas monitor (Make: Swan**®** Environmental Pvt. Ltd. India, Model: GRI-IAT; Sensor make: Membrapor**®**, Switzerland). The monitoring will be carried out in post-monsoon season (October-January). The instrument has an inbuilt geographical positioning system to record the coordinates of sampling site. The ambient air monitoring will be carried out continuously for 24 hours in at identified sites. In case of cluster of sites, a representative site will be identified for gaseous monitoring. The monitor will be placed at more than 3 metres height from ground level at a place having uninterrupted power supply. The data loggers present in the instrument will store the data at set frequency and will be utilized for further statistical analysis. The sampling and monitoring of ambient air for said pollutants will be carried out following the existing guidelines of CPCB, Ministry of Environment, Forests and Climate Change, New Delhi, India [28].

*ii) Monitoring of pollutants in groundwater*. Levels of concerning heavy metals and ions, namely Al, Pb, Hg, Cl^-^ and SO_4_^2-^ will be assessed in representative groundwater samples collected from sources including tube-wells, hand-pumps and open wells from the selected 10 downstream villages (Fig 2). 120 millilitre (mL) each of groundwater samples will be collected from all available and accessible sources in each village. Samples will be collected in high density polypropylene (HDPE) bottles which were pre-cleaned by soaking overnight in 2% nitric acid and washed with double distilled water. Water samples will be collected from handpumps, tube-wells, and open-wells after removing stagnant water using appropriate purging methods [29]. Also, a few water samples will be collected from the Chambal River at specified locations to assess metallic pollutants. Collected water samples will be labeled and transported to the laboratory at room temperature for initial measurement of physiological parameters including pH, total dissolved salts, conductivity, and salinity. Subsequently, the samples will be preserved with trace metal grade nitric acid (HNO_3_, pH <2) and stored at 4°C till analysis within a week.

Analysis of toxic metals, viz. Pb, Hg and Al in the collected groundwater samples will be carried out using inductively coupled plasma optical emission spectroscopy (iCAP**®** 7400 Duo ICP-OES, ThermoFisher Scientific**®** Pvt Ltd) using the EPA method 200.7 (revision 4.4) [30]. Briefly, 6-point calibration standards for each element (Al, Pb, and Hg) will be first prepared in the range of 1–200 parts per billion (ppb) by serially diluting the multi-element stock solution (ICP multi-element standard XIII, Merck, Germany) in 5% HNO_3_ in double distilled water. Specific run parameters and sample introduction system that will be used for analysis of these metals on ICP-OES instrument are summarized in Table 1. The concentration of individual metals in the unfiltered acid preserved groundwater samples (turbidity <1 Nephelometric Turbidity unit), will be determined after successful run of standards (e.g., linear graph with correlation coefficient > 0.999) in the axial view using standard sample introduction setup for Al and Pb, and hydride generation sample introduction system for Hg. The online hydride generation for Hg will be achieved with Enhanced Vapour System sample introduction kit using 0.5% mass by volume (m/v) sodium tetrahydroborate (NaBH_4_) stabilized in 0.5% m/v Sodium hydroxide (NaOH) and 50% volume/volume (v/v) HCl solution [31]. Emission acquisition will be done on the Qtegra**®** ISDS Software at interference free wavelengths of 220.353 nanometer (nm), 184.950 nm, and 396.152 nm for Pb, Hg and Al, respectively. The instrument performance will be checked in between the sample run using quality control samples containing metals of known concentration. Metal levels in each sample will be reported in ppb levels.

**Table 1 pone.0264154.t001:** The ICP OES instrument parameters that will be used during analysis of Pb, Al, and Hg in the groundwater and/or blood samples.

Parameter	Aqueous sample introduction	EVS sample introduction
Pump Tubing	Sample = white/white	Sample = green/green
	Drain = orange/blue	Drain = black/white
		Acid blank = orange/yellow
		Reductant = black/black
Spray Chamber	Baffled cyclonic	Gas Liquid Separator
Nebulizer	V-groove	V-groove
Auxiliary Gas Flow	0.5 Litre per minute	0.5 Litre per minute
Coolant Gas Flow	12 Litre per minute	16 Litre per minute
Nebulizer Gas Flow	0.5 Litre per minute	0.3 Litre per minute
Pump Speed	50 revolutions per minute	30 revolutions per minute
Center Tube	1.5 millimeter	1.5 millimeter
RF Power	1150 Watt	1350 Watt
Exposure Time	Axial view: Ultraviolet light- 15 seconds, Visible light- 15 seconds	Axial view: Ultraviolet light- 15 seconds,Visible light- 15 seconds
	Radial view: Ultraviolet light- 15 seconds, Visible light- 15 seconds	Radial View: Ultraviolet light- 15 seconds,Visible light- 15 seconds

EVS: Enhanced Vapour System sample introduction, Acid blank: 50% v/v HCl; Reductant: 0.5% m/v NaBH_4_ in 0.5% m/v NaOH. Aqueous sample introduction kit was used for analysis of Al and Pb. Hydride generation kit (EVS) was used for analysis of Hg.

Analysis of chloride and sulphate ions will be performed through kit-based colorimetric (AQUACheck chloride testing kit, WT004A, Himedia Laboratories Pvt Ltd, India) and turbidimetric methods (AQUACheck sulphate testing kit, WT043, Himedia Laboratories Pvt Ltd, India), respectively [32, 33]. As per manufacturers’ instruction, detection of sulphate ions will be performed by taking 1 mL of water sample in a test jar to which 5 drops of supplied reagent 043A and one spoonful of reagent 043B will be added. After a gentle mixing, the solution will be incubated for 5–10 minutes at room temperature to allow the reaction to occur. Then, the solution will be diluted to 10 mL and the test jar will be placed on a circular control sulphate disk of colour chart to observe black disk from above and match with the standard sulphate disk to find out sulphate levels as milligram per litre or parts per million by turbidity comparison. Similarly, for detection of chloride, 2 mL of water sample will be taken to test jar and added with spoonful of reagent 04A-1 and two drops of reagent 04A-2. After gentle mixing, reagent 04A-3 will be added drop by drop to this solution until the colour of entire solution will changes to bluish violet. Chloride content of the water sample will then be calculated using the formula:

$$Cl^{-}\left(ppm\right)=50\times Number\;of\;drops\;of\;04A-3\;solution$$

#### Human exposure assessment

Following biomonitoring will be done to assess exposure in the selected participants:

*i) Inhalational CS*_*2*_
*exposure*. Iodine-azide test will be carried out for estimation of CS_2_ exposure of the participants. The iodine-azide test is based on the fact that certain constituents in the urine of persons exposed to CS_2_ catalyze the reaction between iodine and sodium azide [34, 35]. Participants will be asked to provide approximately 50 mL of clean catch spot urine sample in a sterile container which will be stored at -20°C till analysis. Preparation of reagents and buffers as well as the test procedures will be carried out as previously described [34, 36]. The exposure coefficient will be calculated to estimate Carbon disulfide exposure.

*ii) Metal (Pb*, *Hg and Al) exposure*. Blood levels of Pb, Al, and Hg will be examined in a sub-group of the studied population (sample from every tenth participants). For this, 1 mL of whole blood from each participant will be mixed with 6 mL of freshly prepared mixture of concentrated trace metal grade HNO_3_ and hydrogen peroxide (H_2_O_2_) in a ratio 2:1 (v/v) in high-purity polytetrafluoroethylene (PTFE-TFM) vessels. After gentle mixing of reactants, the PTFE-TFM vessels will be arranged in the rotor (24HVT80, Anton PAAR) and digestion will be carried out in the Anton Paar, Multimicrowave PRO Reaction System at 200°C for 15 minutes [37]. After digestion, the solutions resulting from each digested samples will be cooled to 40°C and diluted to 30 mL with distilled water. Blank will also be prepared for each cycle of digestion using distilled water, nitric acid, and hydrogen peroxide mixture. Analysis of Pb, Al and Hg in the digested blood samples will be carried out on ICP-OES (iCAP**®** 7400 Duo ICP-OES, ThermoFisher Scientific**®** Pvt Ltd) system using same run parameters as used for groundwater analysis. Recorded metal levels in each sample will be tabulated in ppb levels.

#### Health assessment

Following health-related data will be collected from all selected participants:

*i) Questionnaire-based collection of data on demography*, *exposure and lifestyle*. A structured questionnaire which has been developed by the researchers will be pilot-tested and thereafter wards used for collection of socioeconomic and demographic details along with information regarding lifestyle factors, occupational and relevant exposure history. The questionnaire will be administered by trained investigators in the local language.

*ii) Anthropometry and blood pressure monitoring*. Height and weight will be measured using stadiometer and weighing scale, respectively and will be used to calculate body mass index (BMI). As per guidelines for Indian population [38], BMI in the range of 18.5–22.9 kilogram per square metre (kg/m^2^) will be considered as normal, 23–24.9 kg/m^2^ as overweight and more than or equal to 25 kg/m^2^ will be considered as obesity. Blood pressure will be measured as per the International Society of Hypertension’s 2020 Global Hypertension Practice Guidelines [39] in sitting position on the left arm using validated electronic blood pressure monitor (Omron**®**), after 5 minutes of rest. Systolic and diastolic blood pressure will be recorded as the mean of last two of three readings taken 1 minute apart. Hypertension will be defined as the study participants having raised systolic and/or diastolic blood pressure (more than or equal to 140 and/or 90 millimetres of mercury i.e. mm Hg, respectively) [38].

*iii) Clinical history and examination*. The information regarding current and previous cardiorespiratory and neurological symptoms will be taken by the physicians from the participants using a clinical proforma. The details regarding the onset, duration, severity of symptoms, diurnal variation, aggravating/relieving factors, and associated symptoms details will be noted. A general physical examination and detailed respiratory, cardiological and neurological examination of all participants will be conducted which will include higher mental function examination, speech assessment, cranial nerve examinations, examination of the motor system and muscle power, examination of the sensory system, reflexes and coordination, and gait assessment, etc. All abnormal findings will be recorded in a pre-designed the clinical proforma.

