**Methods:**

Comprehensive exposure data about the concentrations of relevant pollutants in the ambient air and ground water samples in the study area will be collected over one year. Using stratified random sampling, 3003 apparently healthy adults will be selected from the study area. Sociodemographic and anthropometric information, relevant medical and family history, and investigations including spirometry, electrocardiogram, neurobehavioral tests, and laboratory investigations (complete blood count, lipid profile and random blood glucose) will be conducted. Finally Iodine azide test and heavy metal level detection in urine and blood samples respectively will be conducted in a subset of selected participants to assess individual pollution exposure. Ethics approval has been obtained from the Institutional Ethics Committee of the National Institute for Research in Environmental Health (No: NIREH/IEC-7-II/1027, dated 07/01/2021).

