**Fig 3 pone.0264154.g003:**
[figure not shown]
Map of the study area created by research team to assist in selection of exposure monitoring locations and in participant sampling. [Note: The inset in the map shows the Ujjain district of the central Indian province of MP. Within the Khachrod Tehsil of the Ujjain district, lies the study area of the current project. Considering the Birlagram industrial region as the centre, three concentric circular regions were demarcated based on distance (2, 5 and 10 km from the centre)].

Finally, 2000 participants will be selected from the villages in the northern hemisphere while 1003 will be taken from the villages in the southern hemisphere within the 10km radius comprising a total of 3003 participants. In each hemisphere, a fixed number of villages will be selected randomly from those situated in each of the 0-2km, 2-5km and 5-10km zones. Further in each selected village, using the list of all individuals residing in the villages that will be retrieved from the local authorities as the sampling frame, individuals meeting the eligibility criteria will be randomly invited for participation in the study. Total number of individuals sampled in each village will be proportionate to the total population of the selected village.

Participants will be selected for the study only if they fulfill all the following criteria:

Adults (≥18 years of age) of both genders (except pregnant women),Should have been residing for at least one year in the selected village,No history of neuropsychiatric conditions that might hinder completion of neurobehavioral tests,No history of other conditions that are contraindications for performing Pulmonary function test (PFT) like presence of any active disease (e.g. pulmonary Tuberculosis, active haemoptysis, orofacial pain, acute respiratory infection including COVID-19 i.e. coronavirus disease caused by SARS-Cov-2 virus) or recent history (within previous 1 month) of myocardial infarction/aneurysm/surgery, etc.

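### Hypertension is classified from measured blood pressure alone, so treated participants with readings below the threshold count as not hypertensive

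*Protocol article*

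**What the plan says.** In the Protocol article, Health assessment, item ii, the rule reads: "Hypertension will be defined as the study participants having raised systolic and/or diastolic blood pressure", with the cut-offs given as "more than or equal to 140 and/or 90 millimetres of mercury i.e. mm Hg, respectively". The value classified comes from a single set of measurements: "Systolic and diastolic blood pressure will be recorded as the mean of last two of three readings taken 1 minute apart". The rule has no limb for treatment or earlier diagnosis.

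The Abstract (Methods) says that "relevant medical and family history" will be collected, but the definition does not use it. Item iii of Health assessment describes the clinical history in terms of symptoms: "The information regarding current and previous cardiorespiratory and neurological symptoms will be taken by the physicians". Antihypertensive medication is mentioned nowhere in the article.

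The eligibility list under Sampling strategy covers age, pregnancy, length of residence, neuropsychiatric history and contraindications to spirometry ("No history of other conditions that are contraindications for performing Pulmonary function test (PFT"). Known or treated hypertension is not among the exclusions. The Abstract describes the sample thus: "3003 apparently healthy adults will be selected from the study area".

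**The concern.** A participant with diagnosed hypertension whose readings are below 140/90 on medication goes into the not-hypertensive group. The variable called hypertension then really measures raised blood pressure on the survey day.

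This bears on the fourth objective in the Introduction, the association between pollutant exposure and health effects, because the Discussion lists abnormal blood pressure among the documented effects of CS2. The reported prevalence would leave out treated and controlled cases. In the comparison between exposure groups, those cases would sit in the reference category of the outcome.

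**Working it through.** **What the document allows.** It gives no figure for hypertension prevalence, treatment or control, so there is no stated hypertension result to reproduce. The one related figure, the sample size, does reproduce and does not depend on hypertension. From Sample size calculation: 1.96² × 0.26 × 0.74 × 1.30 × 1.25 / 0.02² = 3002.7, rounded up to 3003, with p taken from ECG abnormality.

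**Formula.** Let P be prevalence under a 'measured or treated' definition, and c the share of those people who are treated and below the cut-offs. The stated rule captures P × (1 − c) and misses P × c. The shortfall is above zero whenever c is above zero.

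**Size.** P and c are assumptions, shown as a range. Counts are out of 3003.

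| P | c | Captured by the rule | Missed (points) | People |
|---|---|---|---|---|
| 20% | 10% | 18% | 2 | 60 |
| 20% | 30% | 14% | 6 | 180 |
| 30% | 10% | 27% | 3 | 90 |
| 30% | 30% | 21% | 9 | 270 |

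The range is therefore 2–9 points. With wider assumptions (P 20–40%, c 5–30%) it is 0.20 × 0.05 = 1 point to 0.40 × 0.30 = 12 points.

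**Effect on an exposure comparison when c is equal across zones.** Assume prevalences of 35% and 25% and c = 20% in both.
- Observed: 0.35 × 0.8 = 28% and 0.25 × 0.8 = 20%.
- The difference falls from 10 to 8 points.
- The odds ratio falls from (0.35/0.65)/(0.25/0.75) = 1.62 to (0.28/0.72)/(0.20/0.80) = 1.56.
- The prevalence ratio stays at 1.40.

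This is modest attenuation.

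**Effect when c differs between zones.** Assume 30% prevalence in both zones, so no true difference.
- c of 10% against 20%: observed 27% and 24%, odds ratio (0.27/0.73)/(0.24/0.76) = 1.17.
- c of 10% against 30%: observed 27% and 21%, odds ratio (0.27/0.73)/(0.21/0.79) = 1.39.

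This shows only what such a gap would do. Nothing in the document says that one exists.

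**Can treated people enter?** The eligibility list does not remove them. Its reference to active disease belongs to the spirometry contraindications. No listed criterion turns the label 'apparently healthy' into an exclusion of treated hypertension.

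**The case against.** The strongest reply has five parts.

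- **Weight.** Hypertension is not a named objective and does not size the study. It stands beside ECG, spirometry, neurobehavioural tests and laboratory values. This stands and limits the severity.
- **Size.** Every prevalence and control figure above is assumed. This also stands: the document fixes the direction relative to a 'measured or treated' definition, but not the amount.
- **Direction against true hypertension.** A reader might infer that the reported prevalence is certainly too low. The document does not support that. Readings are one minute apart and no repeat visit is described, so people raised on one occasion only would be counted as hypertensive, which pushes the other way. The understatement is certain only against a 'measured or treated' definition, and only if some treated and controlled people are enrolled.
- **Exposure gradient.** A reader might go further and infer that the rule will hide or reverse an effect of distance. That needs control to differ by zone. All zones lie within 10 km of one centre, and no section reports differing access to treatment. It remains a possibility, not a finding.
- **Unseen forms.** The questionnaire and clinical proforma are not shown, and medical history is planned, so medication may already be recorded. It cannot be said that the data will be missing. However, the article states the definition in full, and as stated it would not use them.

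It is also tempting to say that continuous blood pressure is biased in the same way. It is not. Treatment lowers readings whether or not a threshold is crossed, so that is a separate effect. The article names regression models for neurological assessments, not for blood pressure, so there is no stated blood pressure model to correct.

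**Conclusion.** The point holds as one of outcome definition. The rule as written places treated participants with readings below the cut-offs among those without hypertension, and eligibility does not keep them out. Relative to a 'measured or treated' definition the shortfall is P × c, or 2–9 percentage points if P is 20–30% and c is 10–30%. Both ranges are assumptions. With equal c across zones the association is modestly weakened. A spurious zone difference requires unequal c, on which the document is silent. The sample size of 3003 is unaffected. The change is worth making, but no central conclusion of the study rests on it.

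**What to change.** 1. For analysis, define hypertension as measured blood pressure at or above the thresholds already stated, or reported current antihypertensive medication.
2. Report the measured-only variable separately under the name 'raised blood pressure'.
3. Make sure that the questionnaire or clinical proforma records current antihypertensive medication. This should be confirmed before fieldwork, because the classification cannot be repaired at analysis if the item is absent.
4. Flag treated participants wherever blood pressure is compared as a continuous variable.

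The cost is one sentence in the definition and, if it is not already there, one history item. The drawback is reliance on self-reported treatment. Showing both variables lets a reader see how much depends on it. The thresholds, the measurement procedure and the sample size stay as they are.

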Letter-digit substitution test (LDST)	Verbal learning	The LDST consists of a worksheet, which has 8 rows and 20 columns and randomly arranged letters in rows and columns. We will follow previously published method to perform LDST. The subject will be first given the instructions to substitute target letters with digits and practice on a separate sheet for 1–2 rows. Then he/she will be instructed to substitute as many letters with digits as possible in 180 seconds [49].	The net score will be obtained by deducting wrong substitutions from the total substitutions attempted [50].
Memory forward and backward test	Forward span: attention efficiency and capacity. Backward span: executive task particularly dependent on working memory.	We will follow previously published methodology [51] to perform this test. A list of random numbers is read aloud and the subject is asked to recall the numbers in the same order (forwards) and then in reverse order (backwards).	The score will be reported as the maximum number of digits correctly produced forwards (forward subscore) and backwards (backward subscore) by the subject.
Serial three subtraction test	Concentration and attention	We will follow previously published methodology [52] to perform this test. The subject will be asked to count the numbers by serial subtractions of three from 20 backwards.	The time to complete the task along with errors will be noted as score [53].
Trail making test (TMT)	Trail making test A: visual attention and processing speed Trail making test B: executive abilities including set shifting and mental flexibility	We will follow previously published method [54] to perform TMT. In Trail A, the subjects are asked to draw lines connecting circled numbers on a page in sequence as quickly as they can. In Trail B, one alternates between numbers and letters.	In each test, the primary score is the time to complete the task.
Finger tapping test (FTT)	Motor functioning, specifically, motor speed and lateralized coordination	We will use a shorter version of Finger tapping test [55]. In this test, the subject’s palm of dominant hand should be immobile and flat on the board, with fingers extended, and the index finder placed on the counting device. The subject taps his index finger on the lever as quickly as possible within a 10 seconds time interval, in order to increase the number on the counting device with each tap. Such five trials are performed with 10 seconds rest interval in-between each trial [55].	The score is the mean score of trials 3–5.

*v) Clinical investigations (PFT and ECG)*. PFT will be conducted using portable spirometer (Cosmed**®** Pony FX) on comfortably seated participants by a trained technician, supervised by a trained physician, following national guidelines [56], to measure forced expiratory volume in first second (FEV_1_), forced vital capacity(FVC), and peak expiratory flow. Of three acceptable spirograms defined as the difference between the two largest FVC and the two largest FEV_1_ measurements are less than or equal to 0.150 litres, the best value for each parameter will be included for analysis. The predicted values for the FVC will be calculated for each subject using Kamat’s Regression equation [57]. For categorizing pulmonary function impairment, cut-off of 80% of predictive FVC and 70% of FEV_1_/FVC ratio will be taken [58].

A portable 12-lead Electrocardiogram device (BPL CardiArt**®** 9108D) will be used to measure electrical activity of the heart following American Heart Association guidelines [59]. Briefly, in a private screened area, ECG recording will be done by previously trained medical staff on the chest and limbs of supine and relaxed participants. Trained physicians will interpret the ECG recording as per standard guidelines [60].

*vi) Laboratory investigations*. A battery of clinical laboratory investigations comprising of Random Blood Glucose, Complete Blood Counts, and Lipid profile (Total cholesterol, High and low density lipoprotein cholesterol, and Triglyceride) will be carried out for all participants of the study. Blood sample collection will be carried out by trained technician according to standard operating procedure in compliance with WHO Best Practices [61].

To undertake the afore-mentioned three tests, briefly, a total of 5 mL sample of venous blood will be collected from the median cubital vein of the participants by trained technician maintaining sterile precautions. 2 mL blood will be collected in ethylene diamine tetra acetic acid vacutainer for complete blood count which will be processed within 4 hours using a fully automated hematology analyzer (Sysmex**®**). 3 mL blood sample will be collected in plain vacutainer from which serum will be separated and stored at -20°C till analysis. The serum will be used for estimation of lipid profile using semi-automated biochemistry analyzer (ERBA**®**). Random blood glucose will be estimated on the spot from a drop of blood at the time of sample collection, using a hand held glucometer (Accu-Chek**®**).

